## Abstract

**Background:**

This protocol describes a study evaluating two ‘Housing First’ programs, Platform 70 and Common Ground, presently being implemented in the inner-city region of Sydney, Australia. The Housing First approach prioritises housing individuals who are homeless in standard lease agreement tenancies as rapidly as possible to lock in the benefits from long-term accommodation, even where the person may not be seen as ‘housing ready’.

**Methods/Design:**

The longitudinal, mixed methods evaluation utilises both quantitative and qualitative data collected at baseline and 12-month follow-up time points. For the quantitative component, clients of each program were invited to complete client surveys that reported on several factors associated with chronic homelessness and were hypothesised to improve under stable housing, including physical and mental health status and treatment rates, quality of life, substance use patterns, and contact with the health and criminal justice systems. Semi-structured interviews with clients and stakeholders comprised the qualitative component and focused on individual experiences with, and perceptions of, the two programs. In addition, program data on housing stability, rental subsidies and support levels provided to clients by agencies was collected and will be used in conjunction with the client survey data to undertake an economic evaluation of the two programs.

**Discussion:**

This study will systematically evaluate the efficacy of a scatter site model (Platform 70) and a congregated model (Common Ground) of the Housing First approach; an examination that has not yet been made either in Australia or internationally. A clear strength of the study is its timing. It was designed and implemented as the programs in question themselves were introduced. Moreover, the programs were introduced when the Australian Government, with State and Territory support, began a more focused, coordinated response to homelessness and funded rapid expansion of innovative homelessness programs across the country, including Common Ground supportive housing developments.

**Electronic supplementary material:**

The online version of this article (doi:10.1186/s12889-015-1700-y) contains supplementary material, which is available to authorized users.

## Background

Rising rates of homelessness have been well documented across industrialised countries, including the USA [1], the UK [2] and France [3]. In keeping with this trend, recent Australian figures indicated an eight per cent increase in national homelessness since 2006; approximately one in every 200 Australians were homeless in 2011 [4]. Alarmingly, it is estimated that Australian homelessness services provide supported accommodation to only 20 per cent of those who are homeless each night [4].

There is strong evidence to suggest that homelessness is associated with physical and mental health status [5,6]. Individuals experiencing homelessness face higher rates of preventable physical health conditions than the general population, including cardiovascular diseases, infectious diseases and unintentional injuries [6,7]. These conditions are associated with poorer nutrition and living conditions, lack of preventative health measures, limited education, as well as increased levels of psychological stress, exposure to violence and mental health conditions [6,7].

Australian and international evidence highlights the heightened prevalence of substance use disorders and other mental health disorders across homeless populations [6,8-12]. 2007 Australian population data revealed that self-reported rates of a mental health disorder in the past year were notably higher for those respondents with a lifetime homelessness history (54%) compared to those respondents who had never been homeless (19%) [13]. Specifically, substance use disorders were the most common mental health condition amongst the homelessness history respondents, with a reported prevalence rate three times greater than the general population (18% vs. 5%) [13]. Taken together, the heightened comorbidities of physical and mental health conditions experienced by individuals who are homeless places them at elevated risk of involvement with both the health and criminal justice systems [9,10,12,14-18].

Evidence suggests that long-term housing provision improves the health and quality of life of people who are homeless [19,20] and yields substantial cost savings across the health and criminal justice systems [21]. The annual whole-of-government savings are estimated to be at least twice as large as the annual cost of delivering these programs, although the evidence also suggests that the costs of homelessness are uneven across the homeless population [15,22].

### The Australian context

Similar to the international community, homelessness was identified as a key concern by the former Australian Government in 2008. To mark this commitment, the Council of Australian Governments set out a White Paper, *The Road Home* [23], with the headline goals of halving overall homelessness and offering supported accommodation to all rough sleepers by 2020.

Since that time, a range of interventions in the form of assertive outreach services and rapid re-housing programs have been introduced across Australia, including in Sydney, New South Wales (NSW), which has the largest metropolitan homeless population in the country [4]. In response to the geographical concentration of homeless individuals in Sydney, the Inner City Assertive Outreach Program (commonly known as Way2Home) commenced operation in 2010 to provide housing and health assistance to chronic rough sleepers. Jointly managed housing and health support teams used an assertive outreach approach to engage with rough sleepers and coordinate their entry into long-term housing models based on the Housing First approach.

### Housing first

Originally developed in the USA, the philosophy of Housing First is to provide chronically homeless individuals with immediate access to permanent housing without first having to meet traditional pre-requisites such as sobriety or treatment compliance. The provision of housing is seen as the first step and is then combined with coordinated support to enable clients to sustain their tenancies and deal with their often complex needs [24].

### Housing first program 1: scatter site

Platform 70 is a Sydney-based Housing First program that commenced in August 2011. The program is government funded to head-lease 70 units of housing stock from the private rental market scattered across Sydney. Clients housed through Platform 70 were provided wrap-around support services to ensure their tenancies were successfully maintained. Accessing housing from the private rental sector (through a community housing head-lease arrangement) is an innovative approach that increases the housing options available to people sleeping rough. The public housing stock has decreased significantly in Australia and demand for public housing from very low income earners, homeless individuals and their supporting agencies far outstrips supply [25]. The private rental housing market represents a critical, but hitherto under-utilised option for transitioning from homelessness, and the immediacy and diversity of the private rental market can assist with achieving rapid access to housing.

### Housing first program 2: congregated site

The second Housing First program which will be examined in this study is Common Ground Sydney, which opened in November 2011. Common Ground provides social housing accommodation with a community housing provider managing tenancies. This socially integrated housing complex comprises 104 apartments, half of which were allocated to individuals with a chronic homelessness history [23] and the other half to priority social housing and affordable housing tenants. On-site extensive health and social support services are available to all tenants, as well as a link to a social enterprise. The Common Ground model has been rapidly expanded across Australia, with nine other Common Ground buildings either under construction or in operation between 2008 and 2013 [26].

### Aims

While the Housing First approach has been evaluated internationally [27,20,28,29] and is being keenly applied in Australia, there has been a paucity of evidence on the effectiveness of Australian adaptations of the approach. Findings from evaluations of individual Housing First programs within Australia have recently been released publicly [30,31], however no study examining more than one of these adaptations with the same methodology has been conducted. Further, evaluations to date have focused largely on housing sustainability rather that incorporating broader measures of health and quality of life. Given this, there remains a pressing need to determine the efficacy of these respective models (Platform 70 [scatter site]; Common Ground [congregated site]) in relation to both housing and health outcomes. In response to this gap in the evidence-base, we have commenced a longitudinal analysis of these two adaptations using a standardised mixed methods approach to examine the changes in housing and health outcomes associated with the respective models.

Specifically, we aim to:Determine whether changes occurred with respect to clients’ housing stability, physical and mental health and treatment rates, psychological distress, quality of life, substance use patterns, and health and criminal justice system contact.Identify the demographic and social characteristics of clients that predicted success in each model. For the purposes of this study, success was defined as sustained tenancy and improved health and well-being outcomes.Calculate the net of ‘cost offsets’ of the two programs; that is, the reduction in measurable health, criminal justice and other costs borne by government as a consequence of the program.

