### Participants, setting and measures

#### Client surveys

Eligibility criteria to participate in the client surveys were that participants had to be at least 18 years old at baseline, were able to provide informed consent, had a history of chronic homelessness (more than six months history of sleeping rough), and were currently housed or waiting for housing with the Platform 70 or Common Ground programs. All individuals housed through these two programs had to firstly be engaged through the Way2Home assertive outreach program, and as such would have received support prior to entering either housing program.

Initially, all eligible clients were asked by their case manager whether they would consent to being approached by a trained researcher to explain the details of the study. All clients who agreed to participate were provided with a Participant Information Statement and Consent Form which they were asked to read and sign. If a participant was unable to read, all information and instructions were read aloud. The survey was then administered by a trained researcher who read the questions to the participant and recorded their responses in a pen and paper format. Upon completion, the survey was sealed in an envelope and returned to the research supervisor for a quality control check (see Additional file 2 for further information on recruitment process).

Surveys were conducted in a neutral public space that was convenient and comfortable for the participant, such as a park, café or an available consultation room at Common Ground. As compensation for their time and travel, participants were offered an AUD$40 food voucher [33]. All researchers completed a three-hour training session on administering the client survey and adhering to an interviewer safety protocol [34]. On average, surveys took 45 minutes to complete.

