### Demographics

Demographic data included sex (male/female), age (years), Indigenous status (yes/no), completed Grade 10 (yes/no), in a relationship (yes/no), number of children, currently employed (yes/no) and cognitive impairment (yes/no). Cognitive impairment was measured using the Montreal Cognitive Assessment (MoCA), which is a standardised screening tool that has been shown to be appropriate for individuals with varying cultural backgrounds, ages and educational levels [36]. Scores range from 0 to 30, with a score of 25 or less indicating a cognitive impairment.

Homelessness and housing history data measures included whether participants had ever experienced the following states of homelessness (yes/no), the total time in each state (12 months or less/more than 12 months), and the age that they first experienced each homelessness state (years): slept rough; emergency accommodation (up to three months); medium to long term accommodation (12 to 24 months); couch surfed; boarding houses or hostels; or in a caravan (other than a holiday). Participants were also asked to quantify how many different periods they had slept rough for six months or more. Lastly, at both baseline and follow-up client surveys, interviewers assisted participants to fill out a housing calendar for the preceding 12 months, which included the type of accommodation and duration of each stay.

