### Data analysis

Given the nature of the housing programs under evaluation, we were limited by the number of clients engaged with each program and therefore did not perform a formal power-based sample size calculation. Instead, we invited all eligible Platform 70 and Common Ground clients to participate in the client survey, and recruitment continued until all eligible clients had either provided consent or declined participation in the research.

Loss to follow-up comparisons that assesses the characteristics of participants in the two programs who completed both baseline and follow-up client surveys (completers) against those who only completed the baseline survey (non-completers) will be made. The purpose of these comparisons is to determine whether there are any key differences between survey completers and non-completers of each program. Other patterns of missing data will be examined to determine if there are potential biases. Appropriate literature that addresses how to deal with missing data and small populations and/or small samples will also be consulted.

To address Aims 1 and 2, a profile of clients engaged with the two housing programs will be constructed, which will include demographics, homelessness history and health status. Multivariate analysis will be undertaken to determine changes over time (baseline to follow-up) in key outcomes, including housing, health status and treatment rates, quality of life, substance use patterns, and contact with the health and criminal justice systems within and across the two programs. Additionally, multivariable logistic regression will be used to identify factors associated with sustained tenancies using SAS version 9.4 software.

Qualitative interviews with clients and stakeholders will be thematically analysed in line with the general inductive approach using NVivo 10 software. The analysis will identify key themes in sustained and failed tenancies. These data will be presented in such a way as to give some indication of the commonality or otherwise of particular views, but will not purport to be representative.

To address Aim 3, the cost to government of mainstream health and criminal justice service use by Platform 70 and Common Ground clients and how this use changed over time will be examined. It will also review the cost of delivering the programs and the extent to which this is offset by a decrease in the cost of mainstream government services use by participants.

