A detailed examination of mainstream services will utilise the health and criminal justice system contact data collected in the client surveys. Associated costs incurred in the 12 months prior to the baseline client survey will be compared with the cost of services used in the 12 months prior to the follow-up client survey. The cost of health and justice services will also be compared with the NSW population average.

The cost of health and justice services used by client survey participants will be estimated by applying the unit cost for each service to reported use. Unit costs will be estimated from publicly available information including the Report on Government Services 2013 [42] and various other reports, including those published by the Australian Institute of Health and Welfare [43-47]. These sources will also be used to estimate average service use and associated cost for the NSW population.

The cost of delivering the Platform 70 and Common Ground programs will be examined with reference to recurrent expenditure for the period in which clients were housed in the program. We shall also consider the range of rental subsidies provided to clients in the two housing models. Funding and expenditure data will be sought directly from the providers of social, health and tenancy management, and administrative services. To estimate the recurrent cost incurred by housing providers to manage and maintain properties, we shall draw on estimates obtained from the Report on Government Services [42]. Platform 70 and Common Ground case workers potentially provide more time to resolving issues associated with their tenancies than is normal. This implies that the average recurrent cost/dwelling is likely to represent a conservative estimate of the cost incurred by housing providers.

Housing providers also incur the capital cost of accommodation. In our cost analysis we will only consider public and community housing capital costs in the Common Ground program as Platform 70 involves the head leasing of privately owned dwellings. The average capital value of public housing and community housing properties available to Common Ground clients will be established and the annualised value of capital employed estimated by applying an opportunity cost of capital of 8% [42] to the average capital value.

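### Aim 3 promises an offset covering health, justice and other government costs, but the costing method covers only health and justice and leaves the housing calendar unused

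*Protocol article*

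**What the plan says.** In the Aims section, the third aim is to calculate the net cost offsets of the two programs. The offset is defined as "the reduction in measurable health, criminal justice and other costs borne by government". That is three categories: health, criminal justice, and other.

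The Data analysis section then says that Aim 3 will be addressed by examining "the cost to government of mainstream health and criminal justice service use by Platform 70 and Common Ground clients" and its change over time. Delivery costs of the two programs are also to be assessed, together with "the extent to which this is offset by a decrease in the cost of mainstream government services use by participants". The detailed examination of those mainstream services "will utilise the health and criminal justice system contact data collected in the client surveys". Unit costs from published government reports are applied to reported health and justice use, and the 12 months before the baseline survey are compared with the 12 months before the follow-up survey.

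Separately, the section on demographics and housing history says that at both surveys interviewers helped participants to "fill out a housing calendar for the preceding 12 months, which included the type of accommodation and duration of each stay". The costing text does not mention this calendar.

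**The concern.** The aim and the method do not have the same scope. A reader of the results will take the reported net offset as the answer to Aim 3, yet one of the three categories in the definition has nothing behind it.

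The gap matters here because these are housing programs. Accommodation that government paid for before a client was housed, such as an emergency or supported bed, is an obvious candidate for the unnamed category, and the study lists emergency and medium to long term accommodation among the homelessness states that it asks about. If use of such places fell between the two windows, the saving is real to government but is not credited. The offset is then too low and the net program cost too high.

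**Working it through.** The document gives no unit cost, no number of accommodation nights and no offset figure, so there is nothing numeric to reproduce. The check sets the cost categories side by side and then works out the direction of the error.

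**Categories in the offset**

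| Category | Named in Aim 3 | Data source in the costing | Unit-cost step |
|---|---|---|---|
| Health | yes | client survey, service utilisation items | yes |
| Criminal justice | yes | client survey, justice contact items | yes |
| Other | yes | none | none |

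**Could another costed item be the third category?** The Data analysis section also covers recurrent expenditure, rental subsidies, tenancy management and administrative costs, and annualised capital for Common Ground. All of these are costs of delivering the programs, not costs avoided. The rental arrears and tenancy damages listed under housing and support program data arise from tenancies and do not measure use of other services. The items in the Service utilisation section are all health or justice contacts.

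**Does the wider phrase about mainstream government services fill the gap?** No. The next paragraph ties the examination of mainstream services to health and justice contact data.

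**Do the time windows match?** Yes. The costing compares the 12 months before each survey, and the calendar covers the preceding 12 months at each survey.

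**Direction.** Write the reductions between the two windows as H (health), J (justice) and A (government-funded homelessness accommodation outside the two programs).

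- Offset with this component: H + J + A
- Offset as planned: H + J
- Difference: A = sum over accommodation types k of u_k × (n_k,before − n_k,after), where u is the unit cost per night and n the number of nights

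If nights fell, A is positive and the planned offset is understated by A. If nights did not change, A is zero. If nights rose, the planned offset is overstated.

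**What limits A.** For a client who had already spent d days in program housing during the baseline window, the baseline nights that could enter A are at most 365 − d. A client housed throughout that window contributes no baseline nights at all. Several statements suggest that d may often be large:

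- Platform 70 began in August 2011 and Common Ground opened in November 2011.
- Baseline surveys ran from November 2012 to May 2013, so the look-back starts between November 2011 and May 2012.
- Clients could enter the study already housed.
- The client populations equal capacity: 70 clients for 70 head-leased units, and 52 clients for half of 104 apartments (104 / 2 = 52).

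No count of clients housed at baseline is given. Eligibility also required more than six months of sleeping rough, and a night on the street uses no bed. A therefore has a formula and a conditional sign, but no computable size.

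**The case against.** The strongest reply is that the Data analysis section states its health-and-justice scope openly, that Aim 3 speaks only of measurable costs, and that the mismatch is therefore loose wording in the aim. Part of this stands: nobody who reads the method would be misled about what is costed. But the calendar stays are measured, by type and duration, so the word measurable does not exclude them. Nor is this a detail lost in condensing a full protocol: the costing text names its unit-cost sources, its windows and an 8% capital charge, and still gives the third category no method.

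It is also fair to say that the calendar's own categories are not listed. Emergency accommodation is named in the lifetime history, so whether the calendar separates government-funded stays is an inference. The fix has to allow for that.

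Four stronger readings are tempting, and the document does not support them:

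- *Funded accommodation is the main thing that housing replaces.* The population is defined by rough sleeping, and nothing shows that a funded bed was the usual alternative.
- *The full cost of housing is charged against the programs.* Capital is counted for Common Ground only, and the recurrent cost per dwelling is itself described as probably conservative.
- *A money figure can be put on the omission.* Neither nights nor prices are given, so any total would only multiply assumptions.
- *Way2Home outreach is wrongly left out.* It is true that "All individuals housed through these two programs had to firstly be engaged through the Way2Home assertive outreach program" and that program cost is taken "with reference to recurrent expenditure for the period in which clients were housed in the program". But Way2Home is a separate service that began in 2010, before either program, and feeds both, while Aim 3 concerns the offsets of the two programs. Leaving it out is consistent with that perspective.

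**Conclusion.** The point holds as a mismatch between the aim and its analysis. Aim 3 names three categories of avoided cost, the method costs two, and data that could supply at least part of the third are collected but not used. If government-funded emergency or supported stays fell between the windows, the offset is understated by their cost.

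The size is unknown and may be small, for the two reasons shown above: long-term rough sleeping, and housing already in place at baseline for some clients. The direction assumes that such stays fell and that government paid for them. The point is worth correcting because the reported figure would otherwise carry a broader label than its content. It does not invalidate the health and justice comparison.

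**What to change.** Apply published unit costs to government-funded homelessness accommodation stays in the housing calendar, in both 12-month windows, and add the change to the health and justice costs as the third category of Aim 3. Exclude Platform 70 and Common Ground tenancy nights: those are already counted as program cost, and pricing every government-funded night would count them twice. Report the net offset with and without this component, and state which calendar categories were treated as government-funded.

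If the calendar categories do not allow such stays to be identified, restate Aim 3 as a health-and-justice offset only and report the result as a partial offset.

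The cost is small. Both survey rounds are described as complete, so this is a change to the analysis and needs no new data collection: a few more unit costs, some coding of calendar entries and one more line in the cost table. The stays are self-reported, as are the health and justice contacts already being costed. The fallback is a change of wording.
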